## Background

Emergence agitation (EA) is a common phenomenon in the early postanesthetic period in children aged 3–9 years, which was first described by Eckenhoff et al. [1] in the early 1960s. The incidence of EA ranges from 10 to 80% [2, 3]. Although EA is short-lived, as it lasts an average of 30 min and is self-limiting [4], it may cause children to be prone to self-injury, interfere with a child’s recovery, increase healthcare costs, present a challenge to pediatric anesthesiologists, and decrease parents’ satisfaction with anesthesia [5–10]. Furthermore, EA is associated with postoperative maladaptive behavioral changes [11] and was recently considered a ‘vital sign’ [12]. Methods to prevent and treat EA have gained increased interest in pediatric anesthesia, but no gold standard method is currently available.

A variety of studies have investigated numerous contributors to EA, but the exact etiology of EA remains unclear. Inhalational agents with low blood solubility and pain are regarded as two significant predisposing factors of EA. The frequency of EA in children has increased due to the growing use of sevoflurane in general anesthesia, and nerve block administration can decrease the amount of sevoflurane used [13]. Pain plays an important role in EA [14–16], and adequate pain control can reduce the incidence of EA [6]. Numerous studies have reported that lumbar plexus block can provide superior analgesia effects that last 14.5 h [17]. Ultrasound technology has increased in popularity in pediatrics for lumbar plexus block because ultrasound guidance can provide direct visualization of the lumbar plexus to ensure both the safety and efficacy of lumbar plexus block [18–20]. However, controversies concerning the effect of nerve block on EA exist [13, 21–23], and trials studying lumbar plexus block on EA have not been performed.

We designed this prospective, randomized, and blinded study in children undergoing elective hip surgery and hypothesized that ultrasound-guided lumbar plexus block may decrease the incidence of EA in children undergoing elective hip surgery. This trial will provide clinical answers to verify our hypothesis and recommendations for clinical practice.

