#### Secondary outcomes

The secondary outcomes are as follows:The severity and duration of EA 30 min after emergence from anesthesia evaluated using the PAED scale.The intensity of postoperative pain evaluated using the Children’s Hospital of Eastern Ontario Pain Scale (CHEOPS) scale.The incidence of postoperative adverse events.

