The operation will be performed at least 15 min after the nerve block. During the operation, anesthesia will be maintained with 60% nitrous oxide, 40% oxygen, and 2% end-tidal sevoflurane. If the increases in heart rate, noninvasive blood pressure, and respiratory rate are greater than 15% from the baseline the values during the operation, the concentration of sevoflurane will be increased by 0.5%. Conversely, if the reductions in heart rate, noninvasive blood pressure, and respiratory rate are greater than 15% of the baseline values during the operation, the concentration of sevoflurane will be reduced by 0.5% [23]. If additional fentanyl is required when the heart rate, blood pressure, and respiratory rate increase by greater than 25% intraoperatively, the patient will be recorded as a failure or an inadequate lumbar plexus block and also be followed up. Immediate complications will be recorded and treated.

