### Intraoperative anesthetic management and postoperative assessment

If the heart rate is reduced to less than 50 beats per min during the operation, then 10 μg/kg atropine will be used. If the blood pressure is reduced by greater than 25% of the baseline value, then 0.1 mg/kg ephedrine will be administered. At the end of surgery, sevoflurane will be discontinued, and the fresh gas flow will be increased to 6 l/min.

After completion of the operation, children will be transferred to the PACU and observed until the end of the study period. ECG results, noninvasive blood pressure, and pulse oximetry will also be measured every 5 min. After recovery of adequate of spontaneous breathing, purposeful movement, and eye opening, the endotracheal tube will be removed.

EA will be assessed using the PAED scale (Table 1) [24] at 0, 5, 10, 20, and 30 min after emergence from anesthesia. The PAED score will be documented by the same well-trained doctor, who will be blinded to the allocation group. The PAED score consists of five psychometric items: eye contact with the caregiver, purposeful action, awareness of surroundings, restlessness, and inconsolability. Each item is scored on a 5-point scale (0–4). The maximum score is 20. EA is defined as a PAED score greater than 10 points [25]. Patients with severe EA (PAED score ≥ 13) [24] will be treated with a bolus of 0.5 μg/kg fentanyl. The incidence of EA, frequency of severe EA, and duration of EA will be documented.

**Table 1 Tab1:** Pediatric Anesthesia Emergence Delirium (PAED) scale

1. The child makes eye contact with the caregiver	
2. The child’s actions are purposeful	
3. The child is aware of his/her surroundings	
4. The child is restless	
5. The child is inconsolable	

Items 1, 2, and 3 are reverse scored as follows: 4 = not at all, 3 = just a little, 2 = quite a bit, 1 = very much, 0 = extremely

Items 4 and 5 are scored as follows: 0 = not at all, 1 = just a little, 2 = quite a bit, 3 = very much, 4 = extremely

Scores for each item are summed to obtain a total PAED score between 0 and 20

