Postoperative pain will be evaluated using the CHEOPS by a blinded observer at 0, 5, 10, 20, and 30 min after emergence from anesthesia in the PACU. The CHEOPS is a pain-scoring method applied for children aged 1–7 years. The scale was established by McGrath et al. [26]. The CHEOPS consists of six items: crying, facial expression, verbalization, torso position, touching of the affected area, and leg movement. The maximum score is 13, and the minimum score is 4 points. Children with CHEOPS score ≥ 4 will be treated with a bolus of 0.5 μg/kg fentanyl.

Hemodynamic changes and complications will be recorded in the PACU and compared between the two groups.

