### Data collection and management

Clinical characteristics include age, gender, weight, body mass index (BMI), ASA grade, duration of surgery, and duration of anesthesia (from induction of anesthesia to the discontinuation of sevoflurane).

Intraoperative data collection will include the following parameters: heart rate, noninvasive blood pressure, respiratory rate, dose of sevoflurane, and collective fentanyl dose.

Postoperative data collection will include the PAED score at every time point, incidence of EA, frequency of severe EA, duration of EA, time of emergence (from discontinuation of sevoflurane to the first response to a simple verbal command), extubation time (from the end of anesthesia to extubation), CHEOPS score at every time point, the incidence of complications and adverse events, and the dose of fentanyl in PACU.

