## Discussion

EA is a frequent problem in children receiving sevoflurane or desflurane anesthesia. Although some researchers have studied the effect of nerve block on EA, the results are uncertain. This trial seeks to determine whether ultrasound-guided lumbar plexus block administered to children undergoing elective hip surgery will result in a significantly reduced incidence of EA. When studying the effect of nerve block on EA, the type of operation performed should be considered because the site of the surgical procedure is significantly related to the frequency of EA [23]. Moreover, Ohashi et al. [23] reported that patients undergoing minimally invasive surgery may not experience sufficient pain for researchers to evaluate the effect of nerve block on EA. We chose orthopedic surgery because the rate of occurrence of EA is the third highest in this field [23], and hip surgery in children is not only a common pediatric procedure but is also associated with intense pain. Thus, we will not underestimate the effect of ultrasound-guided lumbar plexus block on EA. Ultrasound examination has revolutionized pediatric anesthesia, and ultrasound-guided nerve block has become more popular in pediatric orthopedic surgery in recent years given the increased safety and efficacy of the block. Previous trials have studied several superficial nerves. To the best of our knowledge, no study has assessed the effect of lumbar plexus block, which is a relatively deep procedure, on EA.

The results of our study will confirm the effect of lumbar plexus block on EA in pediatric hip surgery and provide clinical evidence for the prevention of EA. If our hypothesis is verified, then ultrasound-guided lumbar plexus block could be recommended as a safe prevention method for EA.

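### The PACU is the only stated place for recording postoperative complications, so the group comparison covers early events only and cannot support a general statement that the block is safe

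*Protocol article*

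**What the plan says.** The Secondary objectives include a between-group comparison of postoperative complications. The matching entry under Secondary outcomes is "The incidence of postoperative adverse events", with no time window and no list of events.

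The section on intraoperative management and postoperative assessment names the place of recording: "Hemodynamic changes and complications will be recorded in the PACU and compared between the two groups". The same section says that "children will be transferred to the PACU and observed until the end of the study period", without saying when that period ends. The PAED and CHEOPS scores are taken "at 0, 5, 10, 20, and 30 min after emergence from anesthesia", so the last scheduled score is at 30 min.

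Two other places mention complications. The block-group section says "Immediate complications will be recorded and treated". The Data collection section lists "the incidence of complications and adverse events, and the dose of fentanyl in PACU" among the postoperative data. Neither describes a check on the ward, at discharge or later.

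The Background states that "lumbar plexus block can provide superior analgesia effects that last 14.5 h", citing earlier studies. The main Discussion says that, if the hypothesis is verified, "ultrasound-guided lumbar plexus block could be recommended as a safe prevention method for EA", and the Discussion paragraph of the Abstract makes a similar statement.

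**The concern.** The stated recording and the intended conclusion do not cover the same period. By the figure the protocol cites, the block should still be acting when the last score is taken, and probably when the child leaves the PACU. Two kinds of event then fall outside the stated collection: those that first appear after PACU discharge, and those that cannot be recognised until the block has worn off, such as a nerve deficit that a working block may mask.

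What is at stake is the safety statement. A low or zero count of block-related complications would partly reflect when the data were collected, and a reader of the final report could take it as evidence of safety. The limitations paragraph concedes short observation, but in the context of EA and its long-term prognosis. It gives no such warning about complications.

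**Working it through.** No sample-size or power formula applies, and 14.5 h is a literature value that cannot be reproduced from the protocol. The check is how far the stated observation reaches into that period.

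**Inputs from the protocol**
- Cited duration of block analgesia: 14.5 h (Background).
- Last scheduled PAED and CHEOPS score: 0.5 h after emergence.
- Block given after induction, with surgery at least 15 min later.
- Patients per group: 50, or 45 after the allowed 10% dropout (Sample size estimation).

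**Assumptions, because the protocol gives no figure**
- The 14.5 h runs from placement of the block.
- Time from block to emergence: 1 to 4 h.
- PACU stay after emergence: 1 to 2 h.

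**Step 1: use one clock.** Dividing the 30 min directly by 14.5 h gives 0.5/14.5 = 3.4%, but this understates coverage. The 30 min starts at emergence, and the block has been acting since before surgery. Both times should be counted from the block.

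**Step 2: last scheduled score, counted from the block.** Time = (block to emergence) + 0.5 h.

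| Block to emergence (assumed) | Last score after block | Share of 14.5 h | Remaining |
|---|---|---|---|
| 1 h | 1.5 h | 1.5/14.5 = 10% | 13 h |
| 2 h | 2.5 h | 2.5/14.5 = 17% | 12 h |
| 3 h | 3.5 h | 3.5/14.5 = 24% | 11 h |
| 4 h | 4.5 h | 4.5/14.5 = 31% | 10 h |

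**Step 3: end of PACU recording.** Complications may be recorded after the last score, so this is the more relevant limit, but the protocol does not state it. On the assumed stays, recording ends between 1 + 1 = 2 h and 4 + 2 = 6 h after the block. That is 2/14.5 = 14% to 6/14.5 = 41% of the cited duration, leaving 12.5 to 8.5 h. For PACU recording to last as long as the cited effect, the stay after emergence would have to be 14.5 − 4 = 10.5 h at the long end of the assumed range and 14.5 − 1 = 13.5 h at the short end.

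**Step 4: what a longer window could and could not show.** With 0 events in n patients, the one-sided 95% upper limit is 1 − 0.05^(1/n).
- n = 50: 1 − 0.05^(1/50) = 5.8%.
- n = 45: 1 − 0.05^(1/45) = 6.4%.

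The chance of seeing at least one event in 50 is 1 − (1 − p)^50, which is 39% at a true rate of 1% and 4.9% at 0.1%. A longer window makes later events observable, but 50 children per group are too few to exclude a rare one.

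**The case against.** The strongest reply is that the protocol never says recording stops at the PACU. Immediate complications in the block group are recorded under a separate statement, the data list sets no place or time limit on complications, and the end of the study period is undefined. The schedule figure and the additional file are not shown, and the full protocol may contain later follow-up. This stands in part. A reader might infer that complications are recorded nowhere but in the PACU, and the immediate-complications sentence contradicts that. It concerns earlier events, however, and adds no later check. The text also does more than leave a detail out: it names the PACU as the place of recording for the comparison and has the children observed there until the study period ends.

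A second reply is that the 14.5 h refers to analgesia in cited studies, not to motor or sensory block under this trial's technique. That is correct, and masking of a nerve deficit is an inference that the protocol does not state. The gap for events after PACU discharge does not depend on it.

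Three stronger readings are tempting and are not supported:
- A reader might infer that the complication objective cannot be answered at all. It is worded for postoperative complications in general, never names nerve injury, and remains answerable for early events.
- A reader might infer that the comparison favours the block at any sample size, because early opioid effects in controls are visible and block harms are hidden. The documents do not show this. Both arms receive fentanyl at induction and both can receive more during surgery and in the PACU. The one extra recording statement is in the block-group section, which would tend to raise the count in that arm.
- A reader might infer that observation covers only 3% of the block's effect. That figure mixes two starting points, and the scoring schedule is not the stated end of complication recording.

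**Conclusion.** The concern holds in limited form. As written, the between-group comparison of complications is valid for the early period in the PACU. It does not capture complications that appear after PACU discharge or that a working block may mask, so it cannot support the general safety statement planned in the Abstract and Discussion.

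On the assumed timings, roughly 10 to 13 h of the cited effect remain after the last scheduled score. The exact gap cannot be computed, because neither the PACU stay nor the end of the study period is defined. The qualitative conclusion would change only if PACU stays ran to ten hours or more, if the block wore off much sooner than the cited figure, or if the material not shown contains a later check. The outcome affected is secondary, but a planned recommendation rests on it, so it is worth correcting.

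**What to change.** Define the adverse-event window in both arms to end at a fixed point after expected block resolution, for example 24 h after the block or discharge, whichever is later. Take later events from routine ward or discharge notes, abstracted by the blinded data collector in the same way in both groups. Report PACU events and later events separately, so that the early comparison remains interpretable on its own.

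State alongside the result that 0 events in 50 would still be compatible with a rate of up to 5.8% (one-sided 95% limit), so rare nerve injury cannot be excluded even with the longer window.

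The cost is a little extra data abstraction per child, with no new procedure and no additional patients. This assumes that the children remain in hospital after surgery, which the protocol does not state. The Study time section says the study has been completed and the Trial status section says it is recruiting, so an amendment may come too late. Abstraction from existing records may then still be possible. If it is not, limit the safety wording in the Abstract and Discussion to the PACU period and name the short complication window as a limitation.

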### Data collection and management

Clinical characteristics include age, gender, weight, body mass index (BMI), ASA grade, duration of surgery, and duration of anesthesia (from induction of anesthesia to the discontinuation of sevoflurane).

Intraoperative data collection will include the following parameters: heart rate, noninvasive blood pressure, respiratory rate, dose of sevoflurane, and collective fentanyl dose.

Postoperative data collection will include the PAED score at every time point, incidence of EA, frequency of severe EA, duration of EA, time of emergence (from discontinuation of sevoflurane to the first response to a simple verbal command), extubation time (from the end of anesthesia to extubation), CHEOPS score at every time point, the incidence of complications and adverse events, and the dose of fentanyl in PACU.

### Sample size estimation

The sample size was determined by a power analysis based on the incidence of EA in our previous pilot study. The incidence of EA of the control group in our pilot study was approximately 42%. We expect that the intervention group will exhibit a 15% reduced incidence of EA. Based on these assumptions, we found that 45 patients per group will provide a power of 80% for detecting differences in EA incidence at a significance level of 0.05. Considering a possible dropout rate of 10%, 50 patients will be included per group.

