There are some limitations in our trial. First, this trial will be conducted in only one center, which may impact enrollment. In addition, the conclusions of our trial may not be applicable to other centers. However, the use of randomization and computer-generated allocation in our trial can reduce the risk of selection bias. In our trial, assessment investigators and data collectors will remain blinded to allocations, which reduces the treatment effect estimate bias. Moreover, standardization of intervention, including ultrasound-guided lumbar plexus block, intraoperative anesthetic management, and postoperative and outcome measurements, will be performed, which can avoid performance bias. In addition, a correct evaluation sample size was obtained according to our pilot study. Another limitation is that our trial assesses EA for only a short time after the operation, and the observation time is relatively short. The long-term prognosis of EA should be assessed in further studies.

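### The 45 per group does not follow from the stated 15% reduction from 42%: power is about 32% if the 15% is absolute and 9% if relative, not 80%

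*Protocol article*

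**What the plan says.** Under Sample size estimation, the protocol article gives every input to its calculation:

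- Control rate: "The incidence of EA of the control group in our pilot study was approximately 42" (per cent).
- Effect: "We expect that the intervention group will exhibit a 15% reduced incidence of EA".
- Result: "45 patients per group will provide a power of 80% for detecting differences in EA incidence at a significance level of 0.05".
- Dropout: "Considering a possible dropout rate of 10%, 50 patients will be included per group".

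The paragraph does not say whether the 15% is absolute or relative, or whether the 0.05 is one- or two-sided. Randomization gives a 1:1 ratio, and Statistical analysis names the chi-square or Fisher's exact test for EA incidence. In the limitations part of the Discussion, the authors add that "a correct evaluation sample size was obtained according to our pilot study".

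**The concern.** A 15-point difference between two proportions near one third is a modest effect, and 45 per group is a small trial for it. A 15% relative difference is smaller still. The stated size looked several times too small on either reading.

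This calculation is the only justification given for recruiting 100 children, and it concerns the primary outcome. If the stated power is wrong, a non-significant result would be read against a claimed 80% power and taken as evidence that the block does not reduce EA. At the stated effect, such a result would in fact be the likely one.

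**Working it through.** **Inputs.** From Sample size estimation: p1 = 0.42, a 15% reduction, alpha 0.05, power 0.80, 45 evaluable per group, 10% dropout. From Randomization: 1:1 allocation. Two-sided testing is my assumption; one-sided results are given as well.

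**Formulas.** With p̄ = (p1 + p2)/2 and d = p1 − p2:

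- n per group = [1.960·√(2p̄(1−p̄)) + 0.842·√(p1(1−p1) + p2(1−p2))]² / d²
- power = Φ{ [d·√n − 1.960·√(2p̄(1−p̄))] / √(p1(1−p1) + p2(1−p2)) }

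**Step 1: the dropout step.** 45/0.9 = 50. This reproduces, so any error lies in the 45.

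**Step 2: 15 points absolute (0.42 vs 0.27).** p̄ = 0.345.

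- √(2 × 0.345 × 0.655) = 0.6723; √(0.2436 + 0.1971) = 0.6639.
- n = (1.3176 + 0.5587)² / 0.0225 = 156.5, so 157 per group.
- Power at 45: (0.15 × 6.708 − 1.3176)/0.6639 = −0.469, giving 32%.

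**Step 3: 15% relative (0.42 × 0.85 = 0.357).** p̄ = 0.3885.

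- √(2 × 0.3885 × 0.6115) = 0.6893; √(0.2436 + 0.2296) = 0.6879.
- n = (1.3510 + 0.5789)² / 0.003969 = 938.4, so 939 per group.
- Power at 45: (0.063 × 6.708 − 1.3510)/0.6879 = −1.350, giving 9%.

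**Step 4: can another method close the gap?**

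| | 42% vs 27% | 42% vs 35.7% |
|---|---|---|
| n per group, two-sided | 157 | 939 |
| n per group, two-sided with continuity correction | 170 | 970 |
| n per group, one-sided | 124 | 740 |
| Power at 45, two-sided | 32% | 9% |
| Power at 45, exact chi-square | 33% | 9% |
| Power at 45, exact Fisher | 26% | 6% |
| Power at 45, one-sided | 44% | 15% |
| Power at 50 (no dropout), two-sided | 35% | 9% |

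Unpooled and arcsine formulas give 33% and 32% for the absolute reading, and 9% for the relative one. The shortfall in sample size is 157/45 = 3.5-fold or 939/45 = 21-fold.

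**Step 5: what effect does 45 per group detect?** Solving the power formula for 80% at two-sided 0.05 gives an intervention rate of 15.6%, a drop of about 26 points. Working forward from 0.42 vs 0.15 (p̄ = 0.285):

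- n = (1.2512 + 0.5127)² / 0.0729 = 42.7, so 43 per group.
- Power at 45: (0.27 × 6.708 − 1.2512)/0.6092 = 0.919, giving 82% (exact chi-square 84%, exact Fisher 76%).

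This scenario is a 27-point drop, or 27/42 = 64% relative.

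**Step 6: precision.** At 42% vs 27% with 45 per group, the 95% CI half-width for the risk difference is 1.96 × √(0.4407/45) = 0.194, about 19 points. That is wider than the 15-point effect.

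**The case against.** The strongest reply is that the number is right and the wording is wrong: the authors may have planned for a reduction to 15%. Step 5 makes this plausible, since 43 is close to 45. If so, the stated power roughly holds and the defect is one phrase. The document alone cannot settle which it is.

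That limits the claim but does not remove it. No section gives a 15% rate for the block group, and the sentence does not read that way. If it was the intent, the published effect is wrong by almost a factor of two (27 points against 15), and an effect of that size needs its own justification. The match is also not unique or exact. For 42% vs 15%, a continuity correction asks for 50 per group and a one-sided test for 34. With Fisher's exact test, which the plan allows, power at 45 falls to 76%.

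A second reply is that a fuller protocol or analysis plan might explain the calculation. That would answer an omission. Here the inputs and the result are all printed and they disagree.

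**Conclusion.** The concern holds. The stated inputs do not yield the stated size on either reading of the 15%. At two-sided 0.05 with 45 evaluable per group, power is about 32% for a 15-point drop (26% to 33% across the methods tried) and about 9% for a 15% relative drop (6% to 9%). The most generous case, an absolute drop tested one-sided, reaches 44%. At the 15-point effect a non-significant result is about twice as likely as a significant one; at the relative effect, about ten times.

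These figures rest on the 42% control rate and 1:1 allocation as stated, and on two-sided testing, which is assumed but does not change the conclusion. That the trial is underpowered is conditional on the effect as written. If the planned rate was 15%, the power is approximately right and the stated effect is wrong. The paragraph needs correcting either way.

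**What to change.** Rewrite the sample size paragraph to give both assumed incidences, the absolute or relative meaning of the reduction, the sidedness and the test. Then follow the original calculation:

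- **If it used a fall to about 15%:** say so (42% vs 15%, 43 per group, about 82% power at 45 by the normal approximation, 84% exact chi-square, 76% Fisher) and justify expecting a 27-point reduction. Use this option only if the original calculation shows that assumption, so that the effect is not fitted to the sample size afterwards.
- **If it used 15 points or 15% relative:** keep that effect, report the true power at 45 evaluable per group (about 32% or 9%), and state that the trial detects a drop of about 26 points with 80% power.

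In either case, delete the Discussion's statement that the sample size is correct. It would also help, though the correction does not depend on it, to commit to reporting the risk difference with its 95% CI and not to read a non-significant result as absence of effect.

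The cost is rewording in two places and, in the second case, a less favourable stated power. No extra patients are asked for. Study time says the study finished in October 2018 while Trial status says it is recruiting; if it has finished, disclosure is the only remedy left, and this fix still applies.
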